## Abstract

**Introduction:**

Atypical hemolytic uremic syndrome (aHUS) is a rare, progressive, and life-threatening form of thrombotic microangiopathy (TMA) which is caused by dysregulation of the alternative complement pathway (AP). Complement inhibition is an effective therapeutic strategy in aHUS, though current therapies require intravenous administration and increase the risk of infection by encapsulated organisms, including meningococcal infection. Further studies are required to define the optimal duration of existing therapies, and to identify new agents that are convenient for long-term administration. Iptacopan (LNP023) is an oral, first-in-class, highly potent, proximal AP inhibitor that specifically binds factor B (FB). In phase 2 studies of IgA nephropathy, paroxysmal nocturnal hemoglobinuria, and C3 glomerulopathy, iptacopan inhibited the AP, showed clinically relevant benefits, and was well tolerated. Iptacopan thus has the potential to become an effective and safe treatment for aHUS, with the convenience of oral administration.

**Methods:**

Alternative Pathway Phase III to Evaluate LNP023 in aHUS (APPELHUS; NCT04889430) is a multicenter, single-arm, open-label, phase 3 study to evaluate the efficacy and safety of iptacopan in patients (*N* = 50) with primary complement-mediated aHUS naïve to complement inhibitor therapy (including anti-C5). Eligible patients must have evidence of TMA (platelet count <150 × 10^9^/l, lactate dehydrogenase ≥1.5 × upper limit of normal, hemoglobin ≤ lower limit of normal, serum creatinine ≥ upper limit of normal) and will receive iptacopan 200 mg twice daily. The primary objective is to assess the proportion of patients achieving complete TMA response without the use of plasma exchange or infusion or anti-C5 antibody during 26 weeks of iptacopan treatment.

**Conclusion:**

APPELHUS will determine if iptacopan is safe and efficacious in patients with aHUS.

aHUS is a rare, progressive, life-threatening form of TMA characterized by microangiopathic hemolytic anemia, thrombocytopenia, and acute kidney failure.^1^, ^2^, ^3^, ^4^ There is limited information on worldwide epidemiology; however, the literature reports incidence as 0.5 to 2/million/yr.^1^^,^^5^ Patients with aHUS have a poor prognosis before the availability of eculizumab, an anti-C5 antibody therapy. In the pre-eculizumab era, approximately 36% to 48% of children and 64% to 67% of adults reached kidney failure and/or death by 3 to 5 years after onset.^6^, ^7^, ^8^

There have been significant advances in our understanding of the underlying pathophysiology of aHUS,^6^ and we now know that uncontrolled activation of the AP is the pathogenic mechanism in most cases of the disease.^4^ The AP is normally constitutively active at low levels and plays an important role in host defense by amplifying the complement response to pathogens.^9^^,^^10^ Ordinarily, activation of the AP is tightly regulated;^7^ however, in aHUS dysregulation results in excessive formation of C3 and C5 convertases and consequent formation of the membrane attack complex (MAC) on the vascular cells mainly in the kidneys, which is key for the disease phenotype, leading to endothelial cell injury, cell detachment and, ultimately, a thrombotic state: thrombus formation, platelet consumption, vascular occlusion, and mechanical hemolysis^2^ (see Figure 1 for further information). In studies of patients with aHUS, approximately 60% have genetic or acquired abnormalities that impair the normal downregulation of the AP.^1^^,^^2^^,^^15^^,^^16^

**Figure 1 fig1:**
[figure not shown]
Iptacopan inhibits activation of the alternative pathway. In complement-mediated aHUS, dysregulation results in excessive formation of C3 and C5 convertases and consequent formation of the membrane attack complex, leading to endothelial cell injury, cell detachment and, ultimately, a thrombotic state: thrombus formation, platelet consumption, vascular occlusion, and mechanical hemolysis.^2^^,^^11^ Iptacopan does not inhibit the activation of the lectin and classical pathways, nor does it inhibit opsonization, formation of C3/C5 convertase, or membrane attack complex via these pathways.^12^, ^13^, ^14^ Iptacopan binds to FB to prevent activity of alternative complement pathway C3 convertases, inhibiting signaling from the alternative complement pathway and activation of the amplification loop. This prevents downstream generation of the alternative complement pathway C5 convertase complex, alternative complement pathway-dependent opsonization, and alternative complement pathway-mediated formation of C3a and C5a anaphylatoxins and membrane attack complex.^13^^,^^14^

The importance of the AP in the pathogenesis of aHUS was confirmed by the dramatic effectiveness of anti-C5 antibody therapy, which decreased the risk of patients developing kidney failure from approximately 70% to 15%.^17^^,^^18^ Therefore, the anti-C5 monoclonal antibodies eculizumab and ravulizumab have become the standard of care (SoC), along with supportive therapy.^18^

Despite the availability of effective treatment, patients may not have optimal quality of life because of residual kidney damage, financial worries given the high cost of therapy, concerns about the risk of infection, and the burden of therapy.^19^ Specifically, current SoC increases the risk of meningococcal infection^20^, ^21^, ^22^ and requires intravenous infusions every 2 to 8 weeks of eculizumab and ravulizumab, respectively, or weekly subcutaneous administration of ravulizumab. Injection site reaction is another concern and, moreover, these treatments are not available in all countries.^23^ With the rarity of the disease and limited specialist centers for treatment of aHUS, this burden is often compounded by the long distances patients need to travel to receive their recurring therapeutic infusions. Therefore, new targeted oral therapies have the potential to address some of the current limitations and will also create treatment choice.

aHUS is an acute disease with many patients presenting with nonspecific clinical symptoms, including fatigue, pallor, shortness of breath, and reduced urine output with or without edema.^2^, ^3^, ^4^ This varying clinical presentation, combined with the absence of diagnostic biomarkers for aHUS leads to difficulty in diagnosing complement-mediated aHUS from other causes of TMA and definitive test results (autoantibodies or genetic testing), which are only positive in approximately 60% of patients, are not typically available for days to weeks after clinical presentation. Therefore, a diagnosis of aHUS remains a clinical one relying on ruling out other forms of TMA,^16^ notably thrombotic thrombocytopenic purpura as well as hemolytic uremic syndrome caused by Shiga toxin-producing *Escherichia coli*. Indeed, other forms of TMA may be due to distinct mechanisms that do not involve complement activation; for example, thrombotic thrombocytopenic purpura, diacylglycerol kinase epsilon pathogenic variants, and methylmalonic aciduria and homocystinuria cblC complementation type do not respond to treatment with the anti-C5 monoclonal antibody eculizumab.^24^^,^^25^ Furthermore, other diseases, such as systemic lupus erythematosus or sepsis, may have clinical and laboratory findings suggesting a diagnosis of TMA. Therefore, one of the challenges of clinical trials involving patients with aHUS is that there is a risk of patients without complement-mediated aHUS being enrolled, which could lead to either a poor response to treatment or spontaneous resolution (“response”) despite inappropriate treatment.^26^, ^27^, ^28^

Iptacopan (LNP023) is an oral, first-in-class, highly potent proximal complement inhibitor that specifically binds FB and inhibits the AP. In a first-in-human study, 80% or greater inhibition of the AP activity was achieved 2 hours postdose for subjects receiving iptacopan at 25 mg or higher doses.^29^ Inhibition of complement FB prevents activity of AP-related C3 convertase and the subsequent formation of C5 convertase and MAC (Figure 1). The advantage of this mechanism is that iptacopan also blocks amplification of both the classical pathway-dependent and the lectin pathway-dependent C5 activation while not blocking the generation of MAC initiated by the classical pathway and the lectin pathway. This is important because it means that MAC-dependent killing of *Neisseria* spp. through activation of the classical pathway will be maintained in immunized individuals.^13^ Moreover, iptacopan may allow for a more effective immune response to meningococcal infection in vaccinated individuals than anti-C5 antibody therapy.^30^ The well-established role of AP dysregulation in aHUS pathophysiology, the positive preliminary results with iptacopan in patients with IgA nephropathy,^31^ C3 glomerulopathy^32^^,^^33^ and paroxysmal nocturnal hemoglobinuria^12^ in phase 2 studies, coupled with the efficacy of approved complement inhibitor therapies in aHUS, provide a strong rationale to evaluate iptacopan directly in a phase 3 study for patients with aHUS.

Here, we describe the rationale and design of the pivotal APPELHUS phase 3 study, which aims to evaluate the efficacy and safety of iptacopan in adult patients with aHUS.

## Methods

### Study Population

Approximately 50 patients naïve to complement inhibitors (including anti-C5 antibody therapy) will be enrolled. All patients are to provide written consent and fulfill all the inclusion criteria and not meet any of the exclusion criteria (Table 1).

**Table 1 tbl1:** Key inclusion and exclusion criteria

Inclusion	Exclusion
Aged ≥18 yrs	Treatment with complement inhibitors, including anti-C5 antibody
Evidence of TMA, including thrombocytopenia, evidence of hemolysis, and acute worsening of kidney function	ADAMTS13 deficiency (<10% activity)
	Shiga toxin-related HUS
	Positive direct Coombs test
Vaccination against *Neisseria meningitidis, Streptococcus pneumoniae* and *Haemophilus influenzae*	Known diacylglycerol kinase mediated HUS
	Identified drug exposure-related HUS
	HUS related to known genetic defects of cobalamin C metabolism
Patients with a kidney transplant are permitted; however, must: (a) have a known history of aHUS before current kidney transplantation, or (b) have no known history of aHUS, and persistent evidence of TMA at least 4 days after modifying the immunosuppressive regimen	Receiving plasma exchange/plasma infusion for ≥28 days before the start of screening for the current TMA
	Bone marrow/hematopoietic stem cell transplantation, heart, lung, small bowel, pancreas, or liver transplantation
	Patients with sepsis, severe systemic infection, COVID-19 infection, systemic infection which confounds an accurate diagnosis or impedes management of aHUS,
	Patients with a history of recurrent invasive infections caused by encapsulated bacteria
	Systemic sclerosis, systemic lupus erythematosus or antiphospholipid antibody positivity or syndrome, or any other autoimmune disease associated with HUS
	Chronic hemodialysis or peritoneal dialysis

ADAMTS13, a disintegrin and metalloproteinase with a thrombospondin type 1 motif, member 13; HUS, hemolytic uremic syndrome; TMA, thrombotic microangiopathy.

Other protocol-defined inclusion/exclusion criteria may apply.

Patients with aHUS reaching kidney failure that requires a transplant have high rates of disease recurrence posttransplant, with the outcome being worse in patients with *CFH, CFB,* and *C3* mutations.^34^^,^^35^ This study will aim for approximately 5 patients who have reached end-stage renal failure and undergone prior kidney transplantation to investigate iptacopan in patients post-transplant with relapsing disease. This should exclude patients with drug-associated TMA.

Diagnosis of aHUS is by exclusion and requires a differential diagnosis workup. Because the study is running in multiple centers worldwide where practice may differ, a patient selection committee has been established to review individual patient eligibility and confirm enrollment into the study. The committee will ensure an independent review of the aHUS diagnosis of each patient in this global study, thereby standardizing any geographic differences which may exist in diagnosing primary aHUS.

### Study Design

APPELHUS (ClinicalTrials.gov Identifier NCT04889430) is a multicenter, single-arm, open-label study to demonstrate the efficacy and safety of iptacopan at a dose of 200 mg twice daily in adult patients with aHUS who are naïve to complement inhibitor therapy (including anti-C5 antibody therapy; Figure 2). At the time of writing, 26 centers are open for patient recruitment in 12 countries with more sites getting ready to open globally (Figure 3).

**Figure 2 fig2:**
[figure not shown]
Study design aHUS phase 3—APPELHUS (NCT04889430). ∗At study completion, patients have the option to roll over into an open-label extension study. aHUS, atypical hemolytic uremic syndrome; bid, twice daily; IA, interim analysis; *N*, number of patients.

**Figure 3 fig3:**
[figure not shown]
Multicenter recruitment sites involved in the aHUS Phase 3 APPELHUS study (NCT04889430). APPELHUS is currently recruiting patients in 26 centers across 12 countries.

The study comprises a screening period lasting up to 7 days during which patients can receive plasma exchange or plasma infusion therapy, followed by a core treatment period where eligible patients will receive iptacopan 200 mg twice daily for 26 weeks. Patients will thereafter continue receiving iptacopan at 200 mg twice daily for an additional 26 weeks as part of the extension period. Patients completing the full 52 weeks and benefiting from treatment as judged by the investigator may be offered posttrial access to iptacopan by participating in an open-label extension study. A summary of key study assessments is provided in Table 2.

**Table 2 tbl2:** Key study assessments

Assessment category	Assessment
Key efficacy assessments	Complete TMA response^a^
	Hematologic parameters
	eGFR and CKD stage
	Patient-reported outcomes (FACIT-fatigue)
Key safety assessments	Vital signs
	Laboratory evaluations in blood and urine
	Electrocardiogram
	Pregnancy and assessments of fertility
	Selected biomarkers related to disease progression
	Safety and efficacy parameters in patients with different aHUS genetic mutations
Other assessments	Health care resource utilization
	The need for hemodialysis or peritoneal dialysis will be monitored by the investigator during the study

aHUS, atypical hemolytic uremic syndrome; CKD, chronic kidney disease; eGFR, estimated glomerular filtration rate; FACIT-Fatigue, Functional Assessment of Chronic Illness Therapy-Fatigue; TMA, thrombotic microangiopathy.

a Complete TMA response is defined as: (1) hematological normalization in platelet count (platelet count ≥150 × 10^9^/l) and lactate dehydrogenase (below upper limit of normal); and (2) improvement in kidney function (≥25% serum creatinine reduction from baseline), maintained for 2 measurements obtained at least 4 weeks apart, and any measurement in between.

### Study Objectives

The primary objective is to assess the impact of iptacopan on TMA response following 26 weeks of treatment. Complete TMA response is a well-defined and accepted end point in clinical trials with aHUS and has been used in most recent clinical studies in patients with aHUS.^27^^,^^36^ The key objectives and endpoints are reported in Table 3.

**Table 3 tbl3:** Key study objectives and related endpoints

Assessment	Objective	End point
Primary objective	To assess the proportion of patients treated with iptacopan achieving complete TMA response^a^ during 26 weeks of study treatment	Complete TMA response^a^ without the use of PE/PI or anti-C5 antibody therapy during 26 weeks of study treatment
Key secondary objectives	To assess the effect of iptacopan on time to complete TMA response	Time to achieve TMA response during 26 weeks of study treatment
	To assess the proportion of patients achieving an increase of ≥2 g/dl from baseline in hemoglobin levels	An increase in hemoglobin of ≥2 g/dl from baseline during 26 weeks of study treatment
	To assess the following at week 26: • The effect of iptacopan on hematological parameters (platelets, lactate dehydrogenase, hemoglobin) • The effect of iptacopan on eGFR, CKD stage, patient-reported overall fatigue severity, and health-related quality of life	Change from baseline in relevant parameters at week 26
	To assess the effect of iptacopan on dialysis requirement status	Proportion of patients on dialysis who no longer require it through 26 weeks of study treatment
	To assess the safety and tolerability of iptacopan	Adverse events/serious adverse events, laboratory parameters, and vital signs

CKD, chronic kidney disease; eGFR, estimated glomerular filtration rate; PE/PI, plasma exchange/plasma infusion; TMA, thrombotic microangiopathy.

a Complete TMA response: see Table 2 for definition.

### Statistical Considerations

#### Primary Efficacy Estimand

The primary analysis of the primary end point is the assessment of the proportion of patients reaching the status of complete TMA response over 26 weeks (core treatment period). The calculated TMA response rate will be compared with a threshold of 30% using a 2-sided 95% confidence interval (CI) for the proportion of complete TMA responders in iptacopan-treated patients based on asymptotic Gaussian approximation with continuity correction method. The 30% threshold was chosen based on 2 historical trials that are comparable in study design, population, and efficacy endpoints (eculizumab,^36^ ravulizumab^27^). The TMA response rates (and 95% CI) based on asymptotic Gaussian approximation with continuity correction method for the eculizumab and ravulizumab trials were 56.1% (39.7%, 72.5%) and 53.6% (39.6%, 67.5%), respectively. Given the single-arm nature of historical trials, it is difficult to hypothesize the actual extent of eculizumab or ravulizumab effect versus placebo. However, the lower boundaries of the 95% CI (∼40%) could be considered as a demonstrated effect over placebo and taken as the reference. A 30% threshold has been chosen to ensure the preservation of approximately 75% of this reference. A lower bound of the CI of ≥30% will demonstrate that iptacopan preserves a significant proportion of the treatment effect compared to that observed with anti-C5 antibody therapies eculizumab and ravulizumab. The primary analysis will account for different intercurrent events as explained in the following:•Dialysis: if a patient requires dialysis during the 26-week treatment period, creatinine values during dialysis (from first day of dialysis through 5 days after the end of dialysis) will be excluded from the analyses. If a patient is on dialysis throughout the 26 weeks where baseline or postbaseline creatinine values are not available for determining the kidney improvement component of complete TMA response, the patient will be considered a nonresponder. For a patient on dialysis on day 1 (or within 5 days prior), baseline creatinine will be the first assessment ≥6 days postdialysis.•Transfusion: platelet values obtained from the day of a platelet transfusion through 3 days after the transfusion will be excluded from the analyses.•Discontinuation of study treatment for any reason: all available efficacy data will be included to calculate TMA response status without imputation.•Plasma exchange/plasma infusion or anti-C5 antibody therapy use during the treatment period: patients will be considered as nonresponders.

The primary analysis will be performed on the full analysis set, which comprises all patients with aHUS (whose eligibility has been confirmed by the patient selection committee) to whom study treatment has been assigned and who have received at least 1 dose of study treatment. The patients discontinued from the study for not meeting the eligibility criteria based on central laboratory or not confirmed to be eligible by the patient selection committee will be excluded from the full analysis set.

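### Once confirmed over a single window of at least 4 weeks, a complete TMA response can be cancelled only by plasma therapy or anti-C5 use, so later death, dialysis or otherwise-managed relapse scores better than one plasma infusion

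*Protocol article*

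**What the plan says.** All references are to the protocol article.

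- **Definition of response (Table 2, footnote a).** Platelets and LDH are normalised and serum creatinine has fallen by at least 25% from baseline, "maintained for 2 measurements obtained at least 4 weeks apart, and any measurement in between". Nothing is required after that window.
- **Summary measure (Primary Efficacy Estimand).** The analysis takes "the proportion of patients reaching the status of complete TMA response over 26 weeks (core treatment period"). This is a status reached at some time, not a status held at week 26.
- **Endpoint (Table 3).** Response is to occur "without the use of PE/PI or anti-C5 antibody therapy during 26 weeks of study treatment".
- **Objective in running text (Study Objectives).** The aim is "to assess the impact of iptacopan on TMA response following 26 weeks of treatment".
- **Intercurrent events (Primary Efficacy Estimand).** Four are listed: dialysis, platelet transfusion, discontinuation, and PE/PI or anti-C5 use. Three of them matter here:
  - "Discontinuation of study treatment for any reason: all available efficacy data will be included to calculate TMA response status without imputation".
  - For dialysis, "creatinine values during dialysis (from first day of dialysis through 5 days after the end of dialysis) will be excluded from the analyses". Nonresponse is reserved for a patient on dialysis throughout the 26 weeks without usable creatinine values.
  - "Plasma exchange/plasma infusion or anti-C5 antibody therapy use during the treatment period: patients will be considered as nonresponders". No limit by timing or amount is given.
- **Rescue (Safety Analyses).** No rescue medication is prespecified; the choice is left to the investigator under local guidelines and availability.

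Neither death nor loss of a confirmed response appears in the list.

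**The concern.** The rules do not rank outcomes in a clinically sensible order. Take two patients who both meet every component on days 14, 28 and 42. One dies at week 12, returns to dialysis, or relapses and is managed without PE/PI or anti-C5: this patient remains a responder. The other receives one plasma infusion at week 24: this patient becomes a nonresponder.

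The trial is open-label and single-arm, and rescue is at the investigator's discretion. The count held against the 30% threshold therefore depends partly on how a relapse was managed and not only on whether it happened. It can also include patients who are dead, on dialysis or in active TMA at week 26, and the primary proportion would not show this.

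**Working it through.** **1. The declared interval and the plan's own figure.** The half-width is z × √(p(1−p)/n) + 1/(2n), with z = 1.96.

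- p = 0.5, n = 50: 1.96 × √(0.25/50) + 0.01 = 0.1386 + 0.0100 = 0.1486.
- p = 0.5, n = 49: 0.1502, above 0.15.

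The plan's N = 50 for a half-width of at most 0.15 is therefore reproduced. The same formula gives the quoted historical intervals, 39.7% to 72.5% and 39.6% to 67.5%, if the counts were 23/41 and 30/56 (inferred from the percentages).

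**2. When a response can be complete.** Visits are on days 1, 7 and 14, then every two weeks to week 26, with laboratory data at all visits (Safety Analyses). A response first seen on day 14 can be confirmed on day 14 + 28 = 42. One first seen on day 7 could be confirmed from day 35, but the next scheduled visit is again day 42. The core period is 26 × 7 = 182 days, so 182 − 42 = 140 days remain (140/182 = 76.9%). Day 42 is the earliest nominal date, not a typical one.

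**3. What each later event does to a confirmed response.**

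| Event after the window | Rule that applies | Status |
|---|---|---|
| Death | None stated; read as discontinuation for any reason, available data used | Responder |
| Return to dialysis | Creatinine values removed | Responder |
| Relapse managed without PE/PI or anti-C5 | None | Responder |
| One use of PE/PI or anti-C5 | Nonresponder rule | Nonresponder |

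**4. How many such patients it takes.** Success needs a lower limit of at least 30%.

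| Responders of 50 | Lower limit |
|---|---|
| 25 (planned 50%) | 35.1% |
| 24 | 33.2% |
| 23 | 31.2% |
| 22 | 29.2% |

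For 23: 0.46 − (1.96 × √(0.46 × 0.54/50) + 0.01) = 0.46 − 0.148 = 0.312. For 22: 0.44 − 0.148 = 0.292. Reclassifying one patient changes the conclusion at 23/50. At 25/50 it takes three, since 24 and 23 still succeed.

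**5. Range under assumed loss.** The article gives no rate for loss of a confirmed response, so these shares are assumptions. With a counted rate of 50%, the sustained rate is 0.50 × (1 − loss). The last column is the exact binomial probability of at least 23 sustained responders in 50.

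| Responders later lost | Sustained rate | P(≥ 23/50) |
|---|---|---|
| 0% | 50% | 76.0% |
| 5% | 47.5% | 63.7% |
| 10% | 45% | 49.8% |
| 20% | 40% | 23.4% |

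The 76.0% in the first row uses the continuity-corrected interval. That it falls below the stated power of more than 80% is a separate matter.

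**The case against.** The strongest defence is that ever-response with a 4-week confirmation is deliberate. Study Objectives calls the endpoint accepted, and Primary Efficacy Estimand derives the 30% threshold from two trials it regards as comparable in efficacy endpoints. If those trials also counted ever-response, a stricter primary rule here alone would tilt the comparison against iptacopan. This stands as a reason not to replace ever-response. It does not explain why death should rank above a plasma infusion.

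A second defence is that a death convention is normally left to the full protocol or SAP, which may contain one. This stands in part: the death limb is inferred from an unlisted event and the discontinuation rule. The dialysis and relapse limbs follow from rules the article does state.

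A third is that later deterioration is reported elsewhere: week-26 changes in platelets, LDH, hemoglobin, eGFR and CKD stage, dialysis status, and summaries of deaths and serious adverse events. That is true, but none of these gives the proportion alive and in complete response. It is also true that relapses treated with PE/PI or anti-C5 are already nonresponse, so the relapse limb is narrow.

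Three stronger readings are tempting and not supported:

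- **That the result cannot answer the stated objective.** Only the running-text sentence says *following* 26 weeks. The abstract and Table 3 say *during*, and the estimand says *over*. The rule fits the formal objective; one word is loose.
- **That about 3.4 dead responders should be expected.** The Discussion cites 4 deaths in 58 patients in the ravulizumab trial, and 4/58 × 50 = 3.4. Those are all deaths in another trial, which the article criticises for enrolling patients without complement-mediated disease. Nothing says that any of them followed a confirmed response.
- **That one patient would decide the trial.** This holds only at exactly 23/50.

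**Conclusion.** The point holds as a flaw in how the stated rules order outcomes. It is not a failure of the trial to address its objective. A confirmed response can be undone only by PE/PI or anti-C5 use, for up to 140 of 182 days, so worse outcomes can score above one plasma infusion and the count depends partly on the choice of rescue.

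How many patients this would affect cannot be computed from the article and may be small. The sensitivity of the conclusion can be computed: one patient at 23/50, three at 25/50. This rests on nominal visit days, the declared continuity-corrected interval with N = 50, and death being read under discontinuation for any reason. The change should be made because it is cheap and the trial is pivotal in a life-threatening disease.

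**What to change.** 1. In the intercurrent-event list under Primary Efficacy Estimand, count death within the 26-week core period as nonresponse, on the same footing as PE/PI and anti-C5 use.
2. Otherwise keep ever-response as primary, for comparability with the 30% threshold. Report the as-written rate as a sensitivity analysis.
3. Prespecify a supplementary estimate: the proportion in complete TMA response at week 26. A patient counts if all components are met at the last core-period assessments at least 4 weeks apart and at any in between, and if the patient is alive, not on dialysis, and without PE/PI or anti-C5 use.
4. Under Study Objectives, change *following* 26 weeks to *during* 26 weeks, to match Table 3.

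The cost is wording and additional tabulation from data already collected. The downside is a possibly slightly lower response rate and a slightly more conservative comparison with the historical trials, whose handling of death is not shown. If the full protocol or SAP already contains a death rule, step 1 reduces to stating it here.

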#### Safety Analyses

Patient safety will be closely monitored by investigators at prescreening, on days 1, 7, and 14, then at biweekly visits until 26 weeks, and monthly visits thereafter. At each visit, physical examination, vital signs (blood pressure, heart rate, pulse rate, respiratory rate, pulse oximetry), and body temperature will be assessed. Electrocardiograms will be recorded at selected visits and laboratory data will be measured at all visits.

Treatment-emergent adverse events, death, serious adverse events, and other significant adverse events, including those leading to treatment or study discontinuation will be summarized by primary system organ class and preferred term.

The use of prespecified rescue medications are not included in the protocol and will be selected at the discretion of the investigator based on local guidelines and availability.

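### The rescue rule names only plasma therapy and anti-C5 while rescue is left open and data after stopping count, so a response on another TMA-directed therapy could be credited to iptacopan

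*Protocol article*

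**What the plan says.** The Primary Efficacy Estimand section lists the intercurrent events and how each is handled. For stopping iptacopan, whatever the reason, "all available efficacy data will be included to calculate TMA response status without imputation". For rescue the rule is: "Plasma exchange/plasma infusion or anti-C5 antibody therapy use during the treatment period: patients will be considered as nonresponders". No other therapy is named. Table 3 gives the endpoint the same scope: complete TMA response "without the use of PE/PI or anti-C5 antibody therapy during 26 weeks of study treatment".

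The choice of rescue is open. Under Safety Analyses, rescue medication is not prespecified and "will be selected at the discretion of the investigator based on local guidelines and availability". The Introduction says of the anti-C5 agents that "these treatments are not available in all countries", and the Figure 3 legend reports recruitment in 26 centers across 12 countries.

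Response itself is a laboratory definition (Table 2): platelet, LDH and creatinine criteria "maintained for 2 measurements obtained at least 4 weeks apart, and any measurement in between". It may be reached at any time in the 26 weeks and need not still hold at week 26. A separate rule makes a patient on dialysis throughout, without usable creatinine, a nonresponder.

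The exclusion criteria in Table 1 speak of complement inhibitors as a class, with anti-C5 antibodies as one member. The rescue rule names only that member.

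**The concern.** Two rules meet here. Stopping iptacopan is handled by treatment policy, so later data count. Rescue is handled as a composite, so it counts as failure, but only for a short list of therapies. Anything off the list falls under the first rule, and a response obtained after it is attributed to iptacopan. Because rescue is chosen locally, the documents give no assurance that it will stay within the list.

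This matters more than usual because the trial has one arm. Its rate is compared with a fixed 30%, so no control group carries the same misattribution. The success rule is also sensitive to one or two patients near its boundary.

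The second part concerns relapse. Two patients with identical laboratory courses (confirmed response, then relapse) can be classified differently because one received plasma therapy or anti-C5 and the other received neither.

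**Working it through.** **1. Which patients are affected.** Applying the stated rules, and reading the treatment period in the rescue rule as the whole 26 weeks:

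| Course within 26 weeks | Plasma therapy or anti-C5 | Status as written |
|---|---|---|
| Never meets the laboratory criteria | given or not | Nonresponder |
| On dialysis throughout, no usable creatinine | given or not | Nonresponder |
| Stops iptacopan, later meets the criteria | given | Nonresponder |
| Stops iptacopan, receives an unlisted TMA-directed therapy, later meets the criteria | not given | **Responder (case 1)** |
| Meets the criteria over 4 weeks, then relapses | given | **Nonresponder (case 2)** |
| Meets the criteria over 4 weeks, then relapses | not given | **Responder (case 2)** |

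Case 1 can include a complement inhibitor that is not an anti-C5 antibody. Case 2 is possible early: Safety Analyses gives visits on days 1, 7 and 14 and then every two weeks, with laboratory data at all visits, so a response over weeks 2 to 6 can be confirmed with 20 weeks remaining (26 − 6 = 20).

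**2. The plan's own precision figure.** Half-width of the continuity-corrected 95% interval at p = 0.5, n = 50:

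1.96 × √(0.5 × 0.5 / 50) + 1/(2 × 50) = 0.1386 + 0.0100 = 0.1486.

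This agrees with the stated maximum of 0.15, so the interval formula is the plan's.

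**3. The success boundary.** Lower limit = p − 1.96 × √(p(1 − p)/50) − 0.01, required to be at least 30%:

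- 21/50: 0.42 − 0.1368 − 0.01 = 27.3%, fail
- 22/50: 0.44 − 0.1376 − 0.01 = 29.2%, fail
- 23/50: 0.46 − 0.1381 − 0.01 = 31.2%, pass

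**4. Effect of misattribution.** The documents give no frequency for case 1, so this is a range under an assumption. Suppose the true rate is 30% and the counted rate is raised by 1, 2 or 3 patients in 50. The exact binomial probability of at least 23 responders out of 50 is then:

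| Added patients | Counted rate | P(success) |
|---|---|---|
| 0 | 30% | 1.2% |
| 1 | 32% | 2.7% |
| 2 | 34% | 5.2% |
| 3 | 36% | 9.4% |

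One added patient takes the error rate just past the nominal one-sided 2.5%; three take it to nearly four times that (9.4 / 2.5 = 3.8).

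**The case against.** Using all data after discontinuation while counting named rescue as failure is a recognised estimand. Counting a confirmed response at any time is the chosen endpoint, and the plan draws its 30% threshold from two historical trials that it describes as comparable in endpoints. Case 1 also needs a chain of events: stopping iptacopan, receiving neither plasma therapy nor anti-C5, receiving something else, then holding all three criteria over at least 4 weeks. The documents name no such alternative therapy as rescue, and the full protocol may restrict concomitant treatment. Finally, a single patient at the boundary decides any binary trial of 50.

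Much of this stands. It makes the problem narrow and its frequency unknown. It does not remove it, because the article states both rules explicitly and leaves rescue open.

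Four stronger readings are tempting and are not supported:

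- *Failure is recognised only through rescue.* The laboratory criteria and the dialysis rule identify failures in every country.
- *Where anti-C5 cannot be obtained, a relapsing patient stays a responder.* Plasma exchange or infusion also triggers nonresponse, so the patient must receive neither. The remark on availability is general background and identifies no trial site.
- *The objective and the endpoint conflict.* The Study Objectives text opens with "The primary objective is to assess the impact of iptacopan on TMA response following 26 weeks of treatment", but the Abstract, Table 3 and the estimand section all describe response within the 26 weeks. The opening sentence is loose wording.
- *Anti-C5 given after iptacopan is stopped escapes the rule.* Table 3 refers to weeks of study treatment, but the dialysis rule in the estimand section speaks of a 26-week treatment period, which favors the wider reading used above.

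**Conclusion.** The point holds in a limited form and is a cheap improvement, not a fatal flaw. As written, a response reached on an unlisted TMA-directed therapy after iptacopan is stopped counts for iptacopan. That error can only raise the rate. For relapse after a confirmed response, the defect is inconsistency: the same laboratory course can be classified either way according to what was prescribed.

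The size cannot be estimated, because the documents give no rate for either case. What can be said is that the boundary lies between 22 and 23 responders, and that, under the assumption of a true 30% rate, 1 to 3 misattributed patients move the probability of success from 1.2% to between 2.7% and 9.4%. A reader might infer that sites without anti-C5 inflate the result most; nothing in the documents shows this.

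Whether stopping for lack of effect should itself be a failure is a debatable estimand choice, and it is not part of this point.

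**What to change.** Change only the counting; the choice of rescue stays as it is.

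1. **Primary analysis.** Keep the nonresponder rule for plasma therapy and anti-C5. Extend it to any complement inhibitor other than iptacopan, and to any other TMA-directed therapy on a prespecified list, when started before the confirmed response is complete. Fix the list before response status is reviewed, since the trial is open-label.
2. **Supplementary analysis.** Report the proportion meeting the complete-response criteria at week 26 without rescue. Present it descriptively and not as a second test against 30%, because that threshold was derived from the any-time endpoint.

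The second item does not change how relapse is counted in the primary analysis. It shows the reader how many confirmed responses were still present at week 26.

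The cost is a wording change in the estimand section. The laboratory values come from visits already planned. Identifying the added therapies needs concomitant medication records, which the article does not describe and which I assume are kept. The reported response rate may be slightly lower.
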